### Recruitment

#### Quantitative study component

The sample size will be based on children available to be recruited during the control and intervention period, which is anticipated to be 180 children (based on an average of 30 new referrals each month to the burn centre). It is anticipated up to 50 health professionals may be eligible to access the intervention, with an estimated 50% turnover of staff in the training and intervention period (as the recruiting centre is a teaching hospital). Health professionals that commence working at the recruiting centre during the intervention period will be informed about the study by a clinician researcher (MS) or research assistant and offered personal log-in details following informed consent.

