### The Responsive CARE intervention—the intervention

The fully automated web-based Responsive CARE intervention consists of four modules (see Table 1), ideally completed sequentially. The intervention package includes a pre- and post-course quiz to self-assess knowledge and allows users to track their progress (see Additional File 1). Interactive elements such as case scenarios allow the user to receive immediate feedback and respond accordingly. Upon completion of the final module, the user is asked to provide course feedback using an automated form (see Additional File 2). Upon completion of all modules, quizzes and survey, the user is able to access an automated certificate of completion.

**Table 1 Tab1:** The modules and their content for the Responsive CARE intervention

Module	Description
1. Understanding paediatric medical traumatic stress	This module explores what is traumatic about medical experiences and what influences an individual’s response to the same experience. It describes typical responses to PMTS and patterns of recovery, including when specialist help is indicated.
2. Introducing the CARE Framework	All healthcare professionals can identify, prevent or minimise the impact of paediatric medical traumatic stress reactions on ill or injured children, their families and themselves. This can be achieved by integrating responsive trauma-informed care into their standard practice throughout all stages of medical care. This module explores how to use responsive trauma-informed care in practice using the evidence-based CARE framework.
3. General skills for applying CARE	This module explores how health professionals can provide responsive trauma-informed CARE. Health professionals are informed about how CARE was designed including using flexible delivery methods and so as to not add additional work or responsibility to a health professional’s routine. Areas of discussion include the following: managing disclosure and transitions in a trauma-informed manner, the importance of reflective practice when considering scope of practice, and how health professionals can provide responsive trauma-informed care even when time is limited. Cultural considerations for responsive trauma-informed care, as well as considerations for children with special education needs are addressed.

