### Primary health professional outcomes

Change in knowledge scores and self-efficacy will be measured using questions designed for the study and recorded as part of the online package (see Additional File 1 and 2).

Secondary and healthcare resource outcomes to be collected at baseline and 3-months post-baseline in the control and intervention period are as follows:
Administered pain relief: the number (percentage) of patients administered first and second line medications will be recorded. The dose of pain relief and other medication for symptom management will also be recorded.Rate and adjunct interventions (e.g. music therapy, counselling) for pain relief or reduction of stress symptoms.Number of psychosocial or mental health referrals: this will be recorded from medical records.Patient attendance rates at booked appointments and patient reminders: the percentage of booked appointments attended will be measured as well as the number of patient reminders sent by text, mail or phone as per standard practice.Time to wound healing: this will be measured using the time taken in days from the burn injury to ≥ 95% of the wound area re-epithelialized with no further wound dressings required. Re-epithelialization will be assessed by experienced burn consultant or specialised burn nursing staff.

In addition, hospitalisation-related resource use and costs will be collected from hospital administrative records for 12-months prior to the control period for each patient and for the 6-months after the intervention period for each patient for informing cost-related modelling for use in future economic evaluations of web-based education platforms.

Sociodemographic and clinical data will be collected from the following:

(1) The Queensland Paediatric Burns Registry or medical records (maintained by the Centre for Children’s Burns and Trauma Research) including percent total body surface area (TBSA), percent full thickness burn, length of time post-burn, spontaneous skin healing versus grafted site, type of burn and length of time to re-epithelialisation.

(2) Patient and/or caregiver self-report using a standard sociodemographics and clinical data form and questionnaires collecting data on household education, employment, income and occupation, scar location, skin type, age, gender and comorbidities

(3) Fidelity of the intervention based on the commencement and completion rate

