#### Patient-centred outcomes

Sociodemographic, clinical and intervention data will be summarised using descriptive statistics (e.g. mean and standard deviation and 95% confidence intervals) and presented for each group separately. Potential confounding variables for the outcomes are considered a priori to be the following: days to re-epithelialisation, percentage maximum burn depth, days post-burn at baseline, type of injury and number of surgical procedures (e.g. skin grafting) and severity of scarring and child traumatic stress symptoms. Potential confounding variables that are identified as significantly different or different to a clinically meaningful extent between the control and intervention group will be controlled for in analyses where appropriate. As this is a feasibility study, the study will likely be underpowered; therefore, quantitative outcomes will be interpreted only as preliminary findings.

Control period participants will be matched with intervention period participants on factors including age, gender, education and total body surface area burned to examine between group differences. Differences in outcomes between the groups will be analysed using generalised linear (mixed) models or equivalent analyses to examine differences at 3-month and 6-months post-procedure or 3-months and 6-months post-burn where applicable, adjusting for the baseline value of the outcomes where appropriate (with terms included for stratification and confounding variables where applicable). A sensitivity analysis will be conducted using imputation techniques to replace non-ignorable data that is considered to be missing at random over the follow-up period, to determine whether bias is likely in the complete case analysis.

Patient-centred outcome data will be stratified by age to coincide with different versions of patient-reported outcome measures for different age groups and caregiver report versus child report.

The mean difference in change scores for health professional’s knowledge and self-efficacy will be calculated for individual questions and analysed using a Wilcoxon paired test (assuming parametric assumptions are not likely to be observable in this relatively small sample).

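### The primary staff outcomes are knowledge scores and self-efficacy, but the only stated analysis tests each question separately, so neither outcome gets a single estimate

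*Protocol article*

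**What the plan says.** Under Primary health professional outcomes, the protocol article states: "Change in knowledge scores and self-efficacy will be measured using questions designed for the study and recorded as part of the online package". The section describing the intervention adds: "The intervention package includes a pre- and post-course quiz to self-assess knowledge".

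The analysis is the last sentence of Data analysis, Patient-centred outcomes. It says that the mean difference in change scores for knowledge and self-efficacy "will be calculated for individual questions and analysed using a Wilcoxon paired test". The reason given is "assuming parametric assumptions are not likely to be observable in this relatively small sample".

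On numbers, Recruitment, Quantitative study component, expects that "up to 50 health professionals may be eligible to access the intervention", "with an estimated 50% turnover of staff in the training and intervention period". The article gives no number of completed pre-post pairs and no significance level for this analysis. The questions themselves are in Additional Files 1 and 2, which are not part of the text at hand.

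**The concern.** The outcome is stated at the level of a score and the analysis at the level of a question. This is not detail left to a later analysis plan: the article does fix the unit of analysis, and fixes it at a level that does not match its own primary outcome. The reason it gives, a small sample, supports a nonparametric test but not question-by-question testing.

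The first study aim concerns staff self-efficacy, and a specific objective seeks preliminary evidence of an effect on staff knowledge. As written, the results would be a set of separate tests with nothing to say whether knowledge or self-efficacy rose overall. A reader would then have to choose between two poor readings: look at one question at a time, with little power, or note that some question reached significance, with an inflated error rate.

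**Working it through.** The article contains no power or sample size figure for this outcome, so there is nothing to reproduce. The mismatch follows from the two passages alone. The figures below only show its size.

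**Inputs**
- From the article: at most 50 eligible staff and 50% turnover. About 60% of knowledge questions were correct in a staff survey cited in the Background. That survey serves only as an anchor for the starting level.
- Assumed: ten right/wrong questions, two-sided 0.05, no adjustment, 60% correct before and 70% after on every question, and 25 or 50 completed pairs.

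**1. What one question can show.** For a right/wrong question the change is -1, 0 or +1. All non-zero ranks are tied, so the Wilcoxon paired test rests only on how the staff who changed split, as a sign test does. For a simple hand calculation, treat the answers before and after as independent:
- share who gain: 0.4 × 0.7 = 0.28
- share who lose: 0.6 × 0.3 = 0.18
- share who change: 0.28 + 0.18 = 0.46, so 25 × 0.46 = 11.5 of 25 staff
- share of changers who gain: 0.28 / 0.46 = 61%, so about 7 of 12

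An exact two-sided sign test on 12 changers needs at least 10 of 12 in one direction: 2 × (66 + 12 + 1) / 4096 = 0.039. Nine of 12 gives 2 × 299 / 4096 = 0.146. The expected 7 of 12 is well short.

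**2. One question against the total.** Simulated with correlated answers within a person, exact sign test for the question and Wilcoxon test for the total of ten:

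| Pairs | One question | Total score |
|---|---|---|
| 25 | about 6% | 42-68% |
| 50 | 14-15% | 78-96% |

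The top of each total-score range assumes no variation shared by all of a person's answers on one occasion. Adding such variation lowers the power of the total. With a 20% share it falls to 37% at 25 pairs and 61% at 50.

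**3. False positives with no true change.** For k independent tests of actual size a, the chance of at least one is 1 - (1 - a)^k.
- If a is exactly 0.05: k = 5 gives 22.6%, k = 10 gives 40.1%, k = 20 gives 64.2%.
- The exact sign test is conservative. Its actual size is about 2% at 25 pairs and 3% at 50. For k = 10 this gives 1 - 0.98^10 = 18% and 1 - 0.97^10 = 26%, in line with simulated values of roughly 20-27%.
- With the normal-approximation Wilcoxon test, each question has size near 5%, and simulation with ten correlated questions gave 35-44%.

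So the figure depends on how the p-value is computed, which the article does not say.

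**4. Any question significant.** With the exact sign test and 25 pairs, the unadjusted chance that at least one of ten questions is significant is 45-52%, similar to the total in several scenarios. With the approximate Wilcoxon test and a larger gain (60% to 75%), it is 84% against 80-82% for the total. After Bonferroni correction it falls to 31%.

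**The case against.** The strongest reply is that this is a feasibility study. The article says it is likely underpowered and limits quantitative results to preliminary findings. No decision rule rests on these tests, and question-level change is useful because it shows which content needs adapting. That stands and lowers the severity. It does not supply the missing estimate, and descriptive question-level results would serve the same purpose without tests.

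A second reply is that multiplicity rules and scoring are usually left to the analysis plan. That also stands, so the absence of an adjustment is not held against the article. The point is the mismatch it states.

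Three stronger readings are tempting and are not supported:
- A reader might infer that item-level testing loses most of the power. The documents cannot show this. Question count, format and completed pairs are not given, and the loss applies to a single question or an adjusted set, not to an unadjusted reading of all questions. With 50 pairs, five-level questions and the larger gain, one question kept about 57-60% of the power of the total. If training changes only a few questions, the advantage of the total shrinks further.
- A reader might combine the 6% power with a 40% false-positive rate. They belong to different calculations: the exact sign test that gives about 6% power gives roughly 20-27% for ten questions.
- A reader might fault a mean difference reported beside a Wilcoxon test. Giving a mean change as description next to a rank test is not an error.

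**Conclusion.** The concern holds as a mismatch between outcome and analysis. The named primary outcomes are knowledge scores and self-efficacy, and the only analysis stated works question by question, so neither gets a single estimate. That part needs no assumption.

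The sizes are conditional on ten right/wrong questions, a 0.05 level, a uniform rise from 60% to 70% correct and 25 completed pairs. Half of 50 is only a working value, since turnover is not the same as non-completion and new starters may also enrol. The sign-test argument does not carry over to graded self-efficacy ratings, for which one question has somewhat more power. The direction is stable: either each test is weak, or the set of tests carries an inflated error rate.

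Severity is minor to moderate.

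**What to change.** Make the primary analysis the paired change in total (or percent-correct) knowledge score. Separately, analyse the paired change in a self-efficacy summary score if its questions can sensibly be combined, and otherwise one self-efficacy question named in advance. Report each as a mean change with a 95% confidence interval, with one optional Wilcoxon signed-rank test. Two tests at 0.05 would carry a combined error of 1 - 0.95² = 9.75% if independent, whatever the number of questions. Report individual questions descriptively, without tests, to show which content needs adapting.

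The cost is a change of wording; the data are already to be collected. The downside is that a total weights study-designed questions equally and can hide a change confined to a few of them. The descriptive question-level results would still show it.

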### Data storage

Information collected as part of this study will be stored in a locked filing cabinet and in password-protected computer files. Any re-identifiable information obtained in this study will remain confidential and securely stored for 5 years as recommended by the National Health and Medical Research Council Guidelines (NHMRC).

## Discussion

Research is needed to evaluate whether web-based educational interventions focused on trauma-informed care practices can be feasibly used in clinical practices, potentially impact on patient outcomes and be cost-effective within real clinical contexts [53]. Through the use of an implementation science theory and logic model of evaluation, the process of translating web-based educational packages that aim to improve clinical care can be more thoroughly examined. Barriers and enablers within the healthcare system or implementation approach can be identified to better understand the uptake of this intervention into routine practice [54].

## Limitations

The use of a pretest posttest study design for feasibility testing of the intervention has limitations, in that pretest posttest studies do not have control over things that might be changing at the same time as the intervention, so outcomes cannot be attributed to the intervention alone [55]. However, in health services research, these study designs can be valuable to inform a more holistic, population-based, ecological systems science that attends to contextual factors and external validity [56].

## Future directions

Identifying which factors are important for successful implementation can support healthcare settings to consider the appropriateness of educational interventions in their setting. It is anticipated that the study findings will inform educational providers in a healthcare context regarding factors to consider in the process of improving and standardising education approaches across a range of clinical care specialist areas.

## Conclusion

A pre-post, mixed methods design will be employed to examine the feasibility and short-term effect, as well as resource use and costs, of a web-based trauma-informed care educational intervention for staff in a tertiary hospital, outpatient clinical practice setting. It is anticipated that use of implementation science theory and logic model of evaluation will provide insights into factors that impact upon the feasibility of the intervention in a clinical practice setting. This knowledge may support other education approaches within healthcare settings related to improving and supporting patients to reduce the risk of healthcare interactions that result in paediatric medical traumatic stress.

## Data Availability

The datasets used and/or analysed during the current study are available from the corresponding author on reasonable request if appropriate permissions are obtained (by those seeking to access the data) from the data custodians with appropriate ethical and governance approvals from Children’s Health Queensland Hospital and Health Service Human Research Ethics Committee who can be contacted at the following email: [contact]. The author MS can be contacted at [contact] for further information regarding access to the dataset.

## Abbreviations

CFIR: Consolidated Framework for Implementation Research
CHU: Child Health Utility
CONSORT: Consolidated Standards of Reporting Trials
FLACC: Face, Legs, Arms, Cry, Consolability
HRQOL: Health-related quality of life
NHMRC: National Health and Medical Research Council
NRS: Numeric rating scale
PMTS: Paediatric medical traumatic stress
PTSD: Post-traumatic stress disorder
QALY: Quality-adjusted life year
SPPBC: Stuart Pegg Paediatric Burns Centre
TBSA: Total body surface area
TIC: Trauma-informed care
TIDieR: Template for Intervention Description and Replication
